#### Confidentiality {27}

In accordance with the legislative provisions in force (articles L.1121-3 and R.5121-13 of the French Public Health Code), people with direct access to source data will take all the necessary precautions to ensure the confidentiality of information relating to the study drugs, research, participants (especially the latter’s names) and results. Like the investigators, these people are subject to a professional duty of confidentiality.

During or after the study, the data collected on the participants will be sent to the sponsor by the investigators (or any other specialist staff) and pseudonymized. The data must in no case show the study participants’ names or addresses.

Data confidentiality will be ensured by coding the participants’ information as follows:

- Each participant’s initials: the first letter of the family name and the first letter of the first name

- A 5-digit code number: the first two digits correspond to the center number and the final three digits correspond to the incremental inclusion number (from 001 upwards)

The sponsor will ensure that each study participant has given his/her written consent to access to his/her personal data required for the study’s quality control procedures.

### Plans for collection, laboratory evaluation, and storage of biological specimens for genetic or molecular analysis in this trial/future use {33}

Blood samples will be collected via venipuncture and arterial lines and then analyzed in our clinical biochemistry laboratory. We shall assay serum creatinine, lactatemia, CRP, BNP, and troponin Ic on POD1, POD2, and POD7. The samples will be discarded shortly afterwards. No biological specimens will be stored for future studies. No genetic or molecular analyses of human DNA are planned.

### Statistical methods

#### Statistical methods for primary and secondary outcomes {20a}

The study’s primary objective is to demonstrate that the incidence of postoperative complications is lower in an interventional group (patients monitored using a hemodynamic algorithm that incorporates the RER) than in a control group (patients treated according to standard practice). To summarize the characteristics of the study population, quantitative variables will be described as the mean ± standard deviation and/or the median [interquartile range]. Qualitative variables will be described as the frequency [95% confidence interval].

##### Analysis of the primary outcome

The null hypothesis will be rejected in favor of the alternative hypothesis (i.e., there is a difference) using a chi-squared test or Fisher’s test, depending on the frequency of complications (*n* < 5 in a cell of the contingency table), with a two-sided alpha risk of 5%.

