### Assignment of interventions: allocation

#### Sequence generation {16a}

Patients will be randomized into the two parallel, open-label groups using Clinsight® software, as implemented by a data manager from the Clinical Research and Innovation Directorate at Amiens University Medical Center. Randomization by minimization will be performed.

The randomization will be stratified:
By centerBy the type of surgery (orthopedic, vascular, or abdominal)

Patients will be randomly assigned to one of the study groups via centralized randomization by minimization, in order to check for stratification factors and balance the size of the groups. This will also make it possible to check patient eligibility and send randomization information to the investigator for each patient.

After entering their username and password, the investigators will connect to the study randomization site on the day of inclusion and check compliance with the inclusion and noninclusion criteria. If no inconsistencies are found, the result of the randomization will be displayed as “standard management” or “RER.”

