#### Concealment mechanism {16b}

Prior to the provision of informed consent, participants (and, if applicable, their legal guardians) will be given full information about the study by the researchers at each study site. The provision of study information will be recorded in the Clinsight® software by the research assistants. After the baseline survey, eligible participants will be randomized 1:1 into two groups.

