#### Methods for additional analyses (e.g., subgroup analyses) {20b}

No additional analyses are planned.

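### The primary test leaves out centre and surgery type, on which allocation is minimised; if these factors are prognostic, the test is mildly conservative and gives up a modest amount of power

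*Protocol article*

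**What the plan says.** Under Sequence generation {16a} the protocol article states: "Randomization by minimization will be performed". It then says "The randomization will be stratified" and lists two factors, centre and type of surgery (orthopedic, vascular or abdominal). Study setting {9} names five sites, so there are 5 × 3 = 15 combinations. Concealment mechanism {16b} gives the ratio: "eligible participants will be randomized 1:1 into two groups".

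The section Analysis of the primary outcome states: "The null hypothesis will be rejected in favor of the alternative hypothesis (i.e., there is a difference) using a chi-squared test", or Fisher's test where counts are small, at a two-sided 5% level. No covariate or stratum enters that test. The section on secondary outcomes gives no adjusted model for the primary outcome either. The item on additional analyses {20b} reads "No additional analyses are planned".

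Sample size {14} rests on the same unadjusted comparison: 50% versus 35%, alpha 5%, power 80%, 170 per arm, with 350 patients planned in total.

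**The concern.** Minimisation makes the arms more alike on centre and surgery type than simple randomisation would. If those factors predict the outcome, the difference between arms varies less from trial to trial. The plain chi-squared statistic is still scaled by the larger variance that simple randomisation implies. Its p-values then tend to be too large, its real size falls below 5%, and some of the precision gained by balancing is not used.

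The primary outcome is a composite that includes ileus, digestive haemorrhage, transfusion, surgical site infection and respiratory events. It is plausible that its rate differs between abdominal, vascular and orthopedic surgery, but the protocol does not say so.

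What is at stake is calibration and efficiency. The margin is small: at 175 per arm the unadjusted power is about 81% for 50% versus 35%, and 50% is the top of the 30 to 50% range that the protocol quotes.

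**Working it through.** **1. The plan's own figure.** With p₁ = 0.50, p₂ = 0.35 and mean 0.425, the per-arm size is

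n = [1.960·√(2·0.425·0.575) + 0.842·√(0.50·0.50 + 0.35·0.65)]² / 0.15² = (1.370 + 0.582)² / 0.0225 ≈ 169.3, rounded up to 170.

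This reproduces the stated 170 per arm. The same formula gives power of 80.2% at 170 and 81.3% at 175 per arm. The stated test and the stated sample size therefore agree with each other.

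**2. Why the size falls.** Let R² be the share of the outcome variance explained by centre and surgery type. If balance on them were perfect, the variance of the difference would shrink by the factor 1 − R². The real size of the unadjusted test would be about 2·[1 − Φ(1.960/√(1 − R²))].

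**3. Simulation.** From the documents: N = 350, 1:1 allocation, five centres weighted by the stated monthly inclusions (2.5 : 1 : 1 : 2.5 : 1), three surgery types, marginal rates of 50% and 35%. Assumed: minimisation with assignment probability 0.8, surgery mix 50/25/25%, and the log-odds SD of each factor. There were 20,000 trials per scenario, with the logistic model fitted to the first 3,000. "CMH" is the Cochran-Mantel-Haenszel test over all 15 cells.

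| Log-odds SD | Control rates by cell | R² | Size by formula | Size: chi² / CMH / logistic | Power: chi² / CMH / logistic |
|---|---|---|---|---|---|
| 0 (nil) | 50% | 0 | 5.0% | 4.7 / 5.0 / 4.8% | 80.7 / 80.1 / 80.8% |
| 0.2 (weak) | 36–61% | 0.019 | 4.8% | 4.6 / 4.8 / 5.4% | 81.2 / 81.0 / 83.3% |
| 0.35 (moderate) | 27–68% | 0.056 | 4.4% | 4.3 / 5.2 / 5.4% | 81.7 / 82.2 / 84.1% |
| 0.5 (moderate) | 20–74% | 0.106 | 3.8% | 3.7 / 5.1 / 4.9% | 82.6 / 84.9 / 84.9% |
| 0.8 (strong) | 9–85% | 0.219 | 2.7% | 2.5 / 5.1 / 4.9% | 83.4 / 88.2 / 89.4% |

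Monte Carlo error is about 0.15 points on size and 0.3 on power for chi-squared and CMH, and about 0.4 and 0.7 for logistic. The formula and the simulated chi-squared sizes agree to within about 0.3 points.

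**4. Second simulation.** A separate run of 4,000 trials with minimisation, at SD 0, 0.2, 0.35 and 0.5, gave chi-squared sizes of 5.0, 5.3, 4.3 and 4.0%. Power for chi-squared / CMH / logistic was 81.2/80.4/81.8%, 80.7/81.2/81.9%, 82.4/83.4/84.9% and 82.5/84.8/85.8%. The gain of logistic over chi-squared is therefore 0.6, 1.2, 2.5 and 3.3 points.

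**5. Cells at the interim.** At n = 175, 15 cells average 175/15 = 11.7 patients. A centre with weight 1 out of 8 has about 175/8 ≈ 22 patients, or about 7 per surgery type if split evenly. In a further simulation of 6,000 runs, with factor effects redrawn each time, the chance of crossing one-sided p < 0.003 at the interim was, for CMH versus chi-squared, 21.2 v 22.8% (SD 0), 21.4 v 23.1% (0.2), 22.4 v 23.0% (0.35) and 23.3 v 22.1% (0.5). The simulation error on these figures is about 0.5 points.

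**The case against.** The case for leaving the plan alone has four parts.

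- **The planned test delivers what was promised.** Any miscalibration is in the safe direction. Chi-squared power was at least 80.7% in every scenario of the main simulation, against 80% planned. The power given up is measured against an analysis that the trial was not sized for. This stands, and it limits the point to calibration and efficiency.
- **The premise is not documented.** A reader might infer that complication rates must differ by surgery type and that the test therefore certainly runs below 5%. The protocol gives only an overall range of 30 to 50%. If neither factor matters, nothing is lost. This also stands.
- **Stratifying is not always better.** A 15-cell CMH test is slightly worse than chi-squared when the factors are not prognostic (80.1 v 80.7%) and about level when they are weak (81.0 v 81.2%). It also tends to do worse at the interim unless heterogeneity is larger. This stands against that choice of method. It does not stand against main-effects adjustment, which showed no loss in any scenario.
- **The full protocol and the analysis plan are not shown.** They may contain adjusted or sensitivity analyses, and the statement that nothing further is planned sits under an item on subgroup and additional analyses. That statement therefore carries little weight. But the article does not leave the primary test open. An adjusted primary test elsewhere would conflict with it, so the wording would need changing in any case.

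**Conclusion.** The point holds as a modest one. Allocation is balanced on centre and surgery type, and the test fixed for the primary outcome ignores both.

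If the factors are prognostic, the unadjusted test is mildly conservative. Its size is about 5% when they are weak or irrelevant, about 4% when moderate and about 2.5% when strong. The power given up against a main-effects adjusted analysis is about 0 to 2, 2 to 3 and 5 to 6 points respectively. These figures rest on assumed differences between cells, an assumed surgery mix and an assumed minimisation probability. The strong case needs control rates spread from 9 to 85% across cells, which is extreme.

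A reader might go further and conclude that the trial is underpowered or its primary result invalid because of this choice. The documents do not support that: type I error is not inflated, and 80% power at 50% versus 35% is met without adjustment.

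**What to change.** Make the primary analysis a logistic regression with treatment, centre and surgery type as main effects. Report a marginal risk difference with 95% CI. Keep the unadjusted chi-squared or Fisher test as a sensitivity analysis.

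Do not use a CMH test over all 15 centre-by-surgery cells as the primary method, least of all at the interim with 175 patients.

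Fix the choice before any unblinded comparison is seen, so that it cannot look data-driven.

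The cost is a change of wording, slightly more analysis work, and an estimate that depends on a model. Both factors are already recorded for randomisation, and the sample size stays at 350.

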##### Analysis of the secondary outcome

The two arms will be compared with regard to the total volume of intraoperative fluids and the length of stay, using Student’s test or the Mann-Whitney test for normally distributed data.

The two arms will be compared with regard to the changes over time in the SOFA score and the serum NT-pro-BNP, troponin TC, CRP, lactate, and creatinine levels, using a mixed-model analysis of variance. Post hoc comparisons will be performed after Hochberg adjustment. If the data are not normally distributed, they will be log-transformed or otherwise transformed.

The intergroup difference in the incidence of each complication (including mortality) will be compared in a chi-squared test or Fisher’s test.

All statistical analyses will be performed using SAS® software (version 9.4). The threshold for statistical significance will be set to *p* < 0.05 for both the primary and secondary outcomes. The statistical criteria for premature termination of the study are listed above in the statistical analysis section (*p* < 0.003).

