##### Cardiovascular complications

Acute systolic heart failure confirmed by echocardiographic impairment of the left ventricular ejection fraction vs. the preoperative baselineAcute right heart failure confirmed by echocardiographic impairment of right systolic and/or diastolic functionAcute pulmonary edema with fluid overload confirmed by a clinical examination and echocardiography and that leads to medical treatmentAcute circulatory insufficiency, defined as treatment with catecholamines (epinephrine, dobutamine, phosphodiesterase inhibitor, levosimendan, and norepinephrine)Postoperative myocardial damage: troponin I or T elevation above the 99th percentileMyocardial infarction, defined as an elevation in cardiac enzymes (creatine phosphokinase myocardial band, troponin T, or troponin I) plus the appearance of a new Q-wave, ST-segment elevation, or ECG repolarization disorderSupraventricular rhythm disorders, defined as the occurrence of atrial flutter or complete arrhythmia by atrial fibrillation and confirmed by ECGVentricular rhythm disorders, defined as the occurrence of ECG-confirmed ventricular tachycardia

Acute renal failure, defined as a postoperative increase of at least 50% and/or 26.5 μmol/l in the creatinine level vs. the preoperative baseline and/or diuresis of less than 0.5 ml kg^−1^ h^−1^ over 6 h (the KDIGO International Society of Nephrology definition) [22]

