The mean length of stay in each group: the postoperative length of stay in the intensive care unit (ICU) (days) and the overall length of hospital stay (the number of days spent in the hospital until discharge)The proportion of patients with complications within the 7 days following surgery in each groupThe mortality rate on POD30 in each groupThe mean total intraoperative IV fluids administered (crystalloids and colloids) in each groupThe mean laboratory criteria (plasma creatinine, lactate, C-reactive protein (CRP), troponin Tc, and brain natriuretic peptide (BNP) and the SOFA score in each group, measured on POD1, POD2, and POD7)

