### Study timeline for participants

### Sample size {14}

According to the literature data, the postoperative complication rate in the target population is between 30 and 50% [24]. The inclusion of 170 patients in each arm would show that RER-based hemodynamic optimization reduces these complications in a clinically significant manner (by a third; from 50% in the control group to 35% in the interventional arm). These calculations were performed with an alpha risk of 5%, a power of 80%, and a complication rate of 50% in the control arm.

Furthermore, an interim analysis is planned halfway through the inclusion process. Hence, the final study population should be 344 patients. Based on these results and after taking account of potential loss to follow-up, we plan to include 350 patients (175 per arm). If 175 patients are included in each arm, the threshold for statistical significance in a one-sided test will be set to *p* < 0.003 (according to the Lan and Demets spending function, using the seqdesign SAS procedure). Premature study termination for efficacy could thus be considered.

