### Data collection and management

#### Plans for assessment and collection of outcomes {18a}

All data will be continuously recorded on an electronic case report form (eCRF) by a clinical data manager who is blinded to the group allocation. The eCRF was created by study investigators. All the information required by the protocol must be recorded as and when it is obtained in the eCRF, and any missing data must be explained:
“NK” for “not known”“ND” for “not determined”“NA” for “not applicable”

Any access to the study data and any changes will be tracked by the Clinsight® software (Ennov Clinical).

Preoperative data
Demographic dataMedical history (high blood pressure, diabetes, kidney failure, etc.), and the indication for surgery (neoplastic disease or not)Preoperative laboratory assessment (including plasma creatinine and CRP levels)Drug treatments (antihypertensive drugs, antidiabetics, diuretics, etc.)Intraoperative data
*Anesthetic data:*IHypnotics, opioids, and muscle relaxants usedIIVolume of fluids (crystalloids and colloids) usedIIINumber of labile blood products used
(b)*Hemodynamic data (every 30 min):*ISAP, DAP, and MAPIIHeart rateIIIBispectral indexIVTemperatureVCardiac outputVIPulse pressure variationVIITotal amount of ephedrine and norepinephrine usedVIIITotal amount of dobutamine usedIXIntraoperative diuresis
(c)*Surgical data:*ISurgical indication and type of surgery (abdominal, vascular, or orthopedic)IIDuration of surgeryIIIVolume of blood lossIVIntraoperative surgical complications

3.Postoperative dataLength of stay in the recovery roomPatient discharge (to a surgical department, the ICU, or the recovery room)Laboratory assessment:IKidney function: serum creatinine and urea levels on POD1, POD2 and POD7, and renal replacement therapyIIBlood lactate and plasma creatinine, CRP, BNP, and troponin Tc on POD1, POD2, and POD7(d)Standard clinical data (heart rate, blood pressure, peripheral O_2_ saturation, and respiratory rate)(e)Diuresis on POD1, POD2, and POD7(f)KDIGO scores on POD1, POD2, and POD7(g)Postoperative complications(h)Length of stay in the ICU and in hospital(i)30-day postoperative mortality

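### The mixed model for postoperative creatinine and CRP names no use of the preoperative values the trial records; adjusting for them is a nearly free gain in precision on two secondary outcomes

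*Protocol article*

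**What the plan says.** Under Analysis of the secondary outcome, the protocol article gives one method for the SOFA score and the laboratory markers. It states that "The two arms will be compared with regard to the changes over time in the SOFA score" and in the markers, including CRP and creatinine, "using a mixed-model analysis of variance". It adds Hochberg-adjusted post hoc comparisons and a transformation if the data are not normal. No covariate is named.

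The list of secondary outcomes in Outcomes {12} defines these variables as group means, "measured on POD1, POD2, and POD7".

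The data list in section {18a} includes "Preoperative laboratory assessment (including plasma creatinine and CRP levels"), so a value from before surgery should exist for both markers. The definition of acute renal failure in Outcomes {12} already uses one of them: it judges the rise "in the creatinine level vs. the preoperative baseline".

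Sequence generation {16a} minimizes on centre and type of surgery only.

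**The concern.** Patients enter with different creatinine and CRP levels. Chronic kidney failure is one of the qualifying co-morbidities, and only dialysis is excluded, so some spread in preoperative creatinine is built into eligibility. If postoperative levels are compared without the preoperative value, that stable spread stays in the standard error of the arm difference, and any chance imbalance at baseline carries into the estimate in proportion to the correlation. The test stays valid, but a real effect on either marker is harder to see. The data that would reduce both problems are already being collected.

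**Working it through.** **The plan's own figure.** The only precision figure in the article is the sample size for the primary outcome: 50% against 35%, two-sided alpha 5%, power 80%. With pooled variance under the null:

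n = [1.960·√(2·0.425·0.575) + 0.842·√(0.5·0.5 + 0.35·0.65)]² / 0.15² ≈ 169.3, rounded up to 170.

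This matches "The inclusion of 170 patients in each arm". It does not bear on creatinine or CRP, for which the article gives neither a standard deviation nor a correlation.

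**Inputs for the check.** 175 patients per arm (Sample size {14}) and three postoperative visits (Outcomes {12}). The correlation rho between the preoperative value and each postoperative value is an assumption, taken over 0.2 to 0.8.

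**Arm difference in level.** Relative to an unadjusted comparison, adjustment multiplies the variance by 1 − rho² at one visit. For the mean of three visits with equal correlation throughout, the factor is 1 − rho² / [(1 + 2·rho)/3]. The unadjusted detectable difference at 80% power is (1.960 + 0.842)·√(2/175) = 0.300 SD; adjustment multiplies it by √(1 − rho²).

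| rho (assumed) | Variance saved, one visit | 175 per arm behaves like | Detectable difference (SD) | Variance saved, mean of three visits |
|---|---|---|---|---|
| 0.2 | 4% | 182 | 0.293 | 9% |
| 0.3 | 9% | 192 | 0.286 | 17% |
| 0.5 | 25% | 233 | 0.259 | 38% |
| 0.7 | 49% | 343 | 0.214 | 61% |
| 0.8 | 64% | 486 | 0.180 | 74% |

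**Chance imbalance.** The standard error of a baseline difference is √(2/175) = 0.107 SD, so a difference of up to 1.96·0.107 ≈ 0.21 SD is ordinary. The part that carries into an unadjusted postoperative difference is rho·0.21: about 0.04 SD at rho 0.2 and 0.15 SD at rho 0.7. The latter is half of the 0.300 SD detectable difference.

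**If the preoperative value is the first repeated measure.** The contrast at a visit is then a change from baseline, with variance proportional to 2(1 − rho), against 1 − rho² with covariate adjustment. The ratio is (1 + rho)/2, so adjustment saves (1 − rho)/2: 35% at rho 0.3, 25% at 0.5 and 15% at 0.7.

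**If the contrast is arm-by-time among the postoperative visits.** In a small simulation (350 patients, three visits, equal correlations), adding baseline as a main effect left the standard error of the POD7-versus-POD1 contrast unchanged: 0.1269 with and without it at rho 0.3, and 0.0818 with and without it at rho 0.7. In the same runs the standard error of the arm difference at the first visit fell from 0.1055 to 0.1008 (rho 0.3) and from 0.1065 to 0.0759 (rho 0.7), in line with the formula.

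**The case against.** A reader might infer that the trial has decided against adjustment and so throws away much of its precision. The article does not support that. It gives one sentence to six variables and lists no fixed effects, covariance structure or time points. The covariates of a secondary mixed model are commonly left to the full protocol or analysis plan, which are not shown. Silence is not a decision, and this part of the objection stands.

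The phrase about changes over time could also mean that the preoperative value is the first repeated measure. That is a fair reading, but it does not remove the gain, because covariate adjustment is still more precise than a change from baseline at any rho below 1.

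The point about the arm-by-time contrast also stands: a mixed model already removes stable differences between patients from it. The gain applies to the arm difference in level on a given day. That is the quantity closest to the outcome definition, which speaks of means in each group.

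The size is not known. A low correlation is plausible for CRP if the operation itself drives the postoperative level, and the saving is then a few per cent. Finally, a renal effect has another route to detection: acute renal failure is defined against each patient's own baseline and is compared between arms.

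**Conclusion.** The point holds as a minor one. The stated method names no use of preoperative creatinine and CRP, and using them as covariates would improve the daily arm comparisons under either ordinary reading of the model. The saving in single-visit variance relative to a comparison of postoperative levels is 4% to 64% over an assumed rho of 0.2 to 0.8. It becomes substantial only from about rho 0.5. A larger gain for creatinine than for CRP is a judgement, not a figure in the article, so confidence in the size is moderate.

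The stronger inference, that the planned analysis is invalid or biased, does not follow: the unadjusted comparison is valid under randomization. The primary outcome and the sample size are unaffected, and only two secondary markers are shown to have a preoperative value on record.

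**What to change.** State that creatinine and CRP on POD1, POD2 and POD7 (log scale where skewed) will be analysed in a mixed model with arm, day, arm-by-day, the preoperative value of the same marker on the same scale, baseline-by-day, and the two minimization factors, centre and type of surgery. Report the adjusted arm difference with its confidence interval on each of the three days. Apply the same rule to any other marker for which a preoperative value turns out to be recorded.

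The cost is a few lines of text, fixed before any analysis by arm, and a few model parameters, which is negligible with 350 patients. No new measurement is needed. The text should also say how a missing preoperative value is handled, so that adjustment does not drop patients from the comparison.
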